## Abstract

Recurrence rates of atrial fibrillation (AF) after pulmonary vein isolation (PVI) are higher in patients with a left atrial low‐voltage area (LVA) than those without. However, the efficacy of LVA guided ablation is still unknown. The purpose of this study—the Efficacy and Safety of Left Atrial Low‐voltage Area Guided Ablation for Recurrence Prevention Compared to Pulmonary Vein Isolation Alone in Patients with Persistent Atrial Fibrillation trial (SUPPRESS‐AF trial)—is to elucidate whether LVA guided ablation in addition to PVI is superior to PVI alone in patients with persistent AF. The Osaka Cardiovascular Conference will conduct a multicenter, randomized, open‐label trial aiming to examine whether LVA guided ablation in addition to PVI is superior to PVI alone in patients with persistent AF and LVAs. The primary outcome is the recurrence of AF documented by scheduled or symptom‐driven electrocardiography (ECG) during the 1 year follow‐up period after the index ablation. The key secondary endpoints include all‐cause death, symptomatic stroke, bleeding events, and other complications related to the procedure. A total of 340 patients with an LVA will be enrolled and followed up to 1 year. The SUPPRESS‐AF trial is a randomized controlled trial designed to assess whether LVA guided ablation in addition to PVI is superior to PVI alone for patients with persistent AF and LVAs detected while undergoing their first catheter ablation.

## INTRODUCTION

1

For patients with paroxysmal atrial fibrillation (AF), pulmonary vein isolation (PVI) to eliminate ectopic beats is the standard approach.^1^, ^2^ For patients with persistent AF, additional ablation after PVI has been considered necessary because persistent AF is usually accompanied by more complex triggers and a more extensive arrhythmogenic substrate.^3^ However, the efficacy and necessity of additional substrate modifications after PVI in patients with persistent AF remains controversial.

Recurrence rates of AF are higher in patients with left atrial low‐voltage areas (LVAs) than in those without.^4^ LVAs may represent fibrosis, as depicted by delayed‐enhanced magnetic resonance imaging,^5^ and are arrhythmogenic.^6^ Therefore, LVA guided ablation can be a tailored to eliminate the LVA arrhythmic substrate. Although several reports on LVA guided ablation have appeared, a number of these were not randomized controlled trials.^7^, ^8^, ^9^, ^10^ Although the superiority of additional complex fractionated atrial electrogram ablation or linear ablation after PVI was not demonstrated by the STAR AF II trial,^11^ some studies have made them a control group.^12^, ^13^, ^14^ The number of patients with an LVA in these studies is small because of their low prevalence (10%) in patients with paroxysmal AF^15^ and in patients with persistent AF (35%).^7^ The number of patients with an LVA in these studies was only 35–159.^7^, ^8^, ^9^, ^10^, ^12^, ^13^, ^14^, ^15^ To determine whether LVA guided ablation in addition to PVI is superior to PVI alone, the standard approach for AF, a sufficient number of cases with LVAs should be used with PVI alone as a control group.

In this multicenter, randomized trial, we aimed to elucidate whether LVA guided ablation in addition to PVI is superior to PVI with respect to the maintenance of sinus rhythm in patients with persistent AF with a sufficient sample size. This trial will compare the efficacy of LVA ablation in addition to PVI with PVI alone in patients with persistent AF and LVAs.

## METHODS

2

### Objective

2.1

The SUPPRESS‐AF trial will examine whether LVA guided ablation in addition to PVI is superior to PVI alone with respect to the recurrence of AF documented by electrocardiography during the 1 year follow‐up period after the ablation procedure.

**FIGURE 1 clc23677-fig-0001:**
[figure not shown]
Study design. AF, atrial fibrillation; AT, atrial tachycardia; ECG, electrocardiogram; LVA, low‐voltage area; PVI, pulmonary vein isolation; PV, pulmonary vein; SVC, superior vena cava

### Eligibility criteria

2.3

The study population will consist of patients with persistent AF undergoing a first‐time ablation procedure. Persistent AF is defined as a sustained episode lasting ≥7 days at enrollment. Inclusion and exclusion criteria are summarized in Table 1. If patients do not have LVAs after consenting to the study, they will be excluded. A signed ethics committee/institutional review board‐approved informed consent form will be obtained from each patient prior to any trial‐related procedure.

**TABLE 1 clc23677-tbl-0001:** Eligibility criteria

Inclusion criteria for enrollment
Patients undergoing a first‐time ablation procedure for persistent atrial fibrillation
Exclusion criteria for enrollment
Patients with left atrial diameter ≥ 55 mm Patients with prior cardiac surgery Patients with valvular atrial fibrillation Patients receiving dialysis Patients aged <20 years Pregnant patients Patients with a history of stroke, transient ischemic attack, or systemic embolism within the past 6 months Patients who are not considered to be suitable candidates by the physician
Inclusion criteria for allocation
Patients with left atrial low‐voltage area
Exclusion criteria for allocation
Patients withdraw their consent Patients who are not considered to be suitable candidates by the physician

### Procedures

2.4

Anti‐arrhythmic drugs will be discontinued for at least five half‐lives before procedures; amiodarone will be discontinued for at least 60 days. The physician will have the choice of using conscious sedation, deep sedation, or general anesthesia during procedures. Transseptal access to the left atrium will be used. Following the procedure, heparin will be administered to maintain an activated clotting time of >300 sec. Multipolar catheters (8 poles minimum) will be positioned in the coronary sinus and the right atrium, and multipolar catheters (10 poles minimum) will be used for mapping and PVI confirmation. Thermocool SmartTouch (Biosense‐Webster Inc., Diamond Bar CA, USA), an ablation catheter sensing contact force, will be used for ablation and mapping. All procedures will be guided using CARTO3 system (Biosense‐Webster Inc.) which is a 3‐dimensional cardiac mapping system. Anticoagulation therapy will be administered for at least 3 weeks before catheter ablation and 3 months after catheter ablation. After that time, it will be continued or stopped at the physician's discretion.

#### Circumferential pulmonary vein isolation

2.4.1

All patients will undergo an initial ipsilateral circumferential PVI. Whether to perform cardioversion before PVI will be left to the discretion of the physicians. An esophageal temperature probe will be used for continuous real‐time monitoring during applications. A Visitag module (Biosense Webster Inc.), which is a real‐time automated display of applications, will be used with settings as follows: catheter stability ≤2 mm for 5 s, contact force ≥5 g (time ≥ 25%), tag size 4 mm in diameter. All radiofrequency applications will be based on the ablation index (AI). Radiofrequency will be delivered until an AI of ≥425 at the anterior wall and ≥ 375 at the posterior wall is achieved. When delivering radiofrequency around the esophagus, AI of ≥300 will be targeted, but target AI will be left to the discretion of the physicians in order to prevent complications. The maximum interlesion distance will be ≤4 mm.^16^ The standard ablation settings will consist of an upper‐temperature limit of 45°C, a radiofrequency power of 30–40 W, and a catheter irrigation flow rate of 17–30 ml/min. The radiofrequency power will be reduced to 25 W according to esophageal temperature. The success of PVI will be defined as the achievement of a bidirectional block in all PVs. The success of PVI will be reconfirmed at the end of the procedure, a minimum of 20 min after the initial success of PVI. If conduction in the LA and/or PV reappear, reisolation will be performed. Intravenous administration of adenosine triphosphate may be used to detect unablated foci at the discretion of the physician to confirm persistent PVI. If ATP reveals dormant conduction at sites in which the earliest activation is transiently observed on the circular mapping catheter, these sites will undergo further ablation, with confirmation by ATP infusion.

#### Left atrial voltage mapping

2.4.2

After PVI, a detailed left atrial bipolar voltage mapping will be performed with pacing at a rate of 100 ppm on the high right atrium. If AF persists after PVI, electrical cardioversion will be used to restore the sinus rhythm. If sinus rhythm is not maintained, ablation of the right atrium (e.g., superior vena cava isolation, right atrial non‐PV trigger ablation) will be performed. The settings for ablation of the right atrium will be left to the physicians. If sinus rhythm is not obtained after ablation of the right atrium, the patient will be excluded. Ablation of the LA in addition to PVI to maintain sinus rhythm will not be performed to avoid any effect on LVAs. For left atrial bipolar voltage mapping, a multipolar 1 mm electrode catheter with a magnetic sensor will be used (Pentaray or Lasso Nav, Biosense‐Webster Inc., Diamond Bar CA, USA). The point acquisition will be performed with a CONFIDENCE® module (Biosense‐Webster) with the following settings: cycle length range ± 30 msec, local activation time stability 3 msec, position stability 2 mm, density 1 mm, and tissue proximity index off. Fast anatomical mapping volume will be 17 on a scale of 1–20 and voltage mapping with respiration correction will be performed at such a density that the color threshold will be 10 mm. Additional mapping with an ablation catheter will be recommended at sites that are difficult to record with a multipolar 1 mm electrode catheter. When mapping with an ablation catheter, contact force ≥3 g will be required. An LVA will be defined as <0.5 mV. Patients with a total of LVA ≥5 cm^2^ will be randomized to either LVA guided ablation in addition to PVI or PVI alone. Patients with a total area of LVAs <5 cm^2^ will be excluded.

#### Low‐voltage area guided ablation

2.4.3

Cluster ablation for the whole LVA will be performed in patients allocated to LVA guided ablation in addition to PVI. LVAs in the posterior wall may be isolated by linear ablation to avoid esophageal injury. The Visitag module will be used with the following settings: catheter stability ≤2 mm for 5 s, contact force ≥5 g (time ≥ 25%), tag size 6 mm in diameter. Radiofrequency will be delivered to the LVA until an AI of ≥350 and the distance between the tags will be <6 mm. At the discretion of the physician, avoidance of ablation near Bachmann's bundle or near the His bundle will be acceptable if there are concerns they will be injured. The area of residual LVAs that are not ablated will be calculated. Scar areas are not included in the residual LVA.

#### Procedure after low‐voltage area guided ablation or PVI

2.4.4

Following LVA guided ablation in addition to PVI or PVI alone, tachyarrhythmia inducibility will be evaluated using 10‐s burst pacing from the coronary sinus and right atrium at the maximum current output (20 mA), beginning with a cycle length of 400 ms and decreasing to 200 ms. Isoproterenol administration will be used to evoke non‐PV AF triggers. Physicians will perform focal ablation of AF triggers or isolate AF triggers, and ablate to block the cavotricuspid isthmus (CTI) in cases with inducible CTI‐dependent atrial flutter (AFL). Ablation for clinical coexisting tachyarrhythmias such as AFL, atrial tachycardia, and supraventricular tachycardia will also be performed. Physicians will confirm PVI stability by checking the disappearance of the potential in the PV > 20 min after the initial PVI and finish the procedure.

#### Antiarrhythmic drugs and repeat ablation after the ablation

2.4.5

The blanking period after the protocol therapy will be 3 months. AF during this period will not be considered as a recurrence. Anti‐arrhythmic drugs will be strongly recommended not to use after 3 months of the ablation.

Repeat ablation will be performed for recurrent of AF at the discretion of the investigators. During repeat ablation procedures, reisolation of reconnections to the PV and voltage mapping after reisolation of the PV will be required. In patients with PVI alone, LVA guided ablation will not be performed. In patients with LVA guided ablation in addition to PVI, repeat LVA guided ablation may be performed. In patients in both groups, ablation other than LVA guided ablation including linear ablation can be performed at the discretion of the physician.

#### Collection of clinical and follow‐up data

2.4.6

Before ablation, baseline data, information on AF, previous history, and medication history will be collected, and blood tests, transthoracic echocardiography, and 12‐lead ECG will be acquired. Detailed data on the first ablation procedure will be collected. A medication assessment and 12‐lead ECG will be performed at discharge. Adverse events will be collected from the first procedure to 6 months after the first ablation procedure.

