#### Follow‐up schedule

2.4.7

Patients will be followed at 3, 6, and 12 months after ablation. A 12‐lead ECG, Holter ECG, medication assessment, and blood tests will be acquired at 6 and 12 months. Transthoracic echocardiography will be performed at 12 months. Twice‐daily 30 s rhythm checks and symptom‐driven checks will be performed with portable ECG from 6–12 months.

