#### Study endpoints

2.4.8

The primary endpoint of the study will be the recurrence of AF documented by scheduled or symptom‐driven ECG tests during the 1 year follow‐up period after the index ablation procedure. “Recurrence of AF” is defined as the documentation of any atrial arrhythmia including AF, AFL, and/or AT lasting ≥30 s by 12‐lead ECG or other appropriate tests. The endpoint will be determined by the endpoint committee, which will be composed independently of protocol developers, data and safety monitoring board, clinical research funders, investigators, subcontractors, and collaborators.

Secondary endpoints will include death from any cause, symptomatic cerebrovascular stroke, bleeding events, recurrent AF after repeat ablations, and any periprocedural adverse events. Bleeding events are defined as major bleeding in the ISTH bleeding criteria^17^ and bleedings needing for hospitalization.

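### Adverse event collection stops at month 6 while follow-up and discretionary repeat ablation continue to month 12, so complications of later repeat procedures fall outside the only stated collection window

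*Protocol article*

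**What the plan says.** Collection of clinical and follow-up data (2.4.6) sets the collection rule: "Adverse events will be collected from the first procedure to 6 months after the first ablation procedure". The same section promises detailed procedural data for the first ablation only. No other section states a window for collecting safety data.

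Follow-up is longer. The Abstract states: "A total of 340 patients with an LVA will be enrolled and followed up to 1 year". The Follow-up schedule (2.4.7) states: "Patients will be followed at 3, 6, and 12 months after ablation". The primary endpoint in Study endpoints (2.4.8) also covers 1 year.

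The safety endpoints carry no time limit: "Secondary endpoints will include death from any cause, symptomatic cerebrovascular stroke, bleeding events, recurrent AF after repeat ablations, and any periprocedural adverse events". The Abstract lists among the key secondary endpoints "bleeding events, and other complications related to the procedure", again without a window.

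On repeat procedures (2.4.5): "Repeat ablation will be performed for recurrent of AF at the discretion of the investigators". No time limit is given. Repeat low-voltage-area ablation is allowed in the combined arm and ruled out in the PVI-alone arm.

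**The concern.** The trial's full name puts safety beside efficacy. As written, efficacy would be judged over 12 months and general adverse events over 6.

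The months left out are those in which many repeat procedures could be expected. AF in the first 3 months does not count as a recurrence ("The blanking period after the protocol therapy will be 3 months"). After discharge, the scheduled 12-lead and Holter ECGs are listed only for months 6 and 12, and portable ECG monitoring starts at month 6. Apart from recurrences found by symptoms or unscheduled tests, detection therefore begins about when adverse event collection closes. A complication of the repeat ablation that follows would not be collected under the stated rule.

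The loss also need not be balanced. The arms are planned to differ in recurrence and are allowed different lesions at a repeat procedure. Because the trial is open-label, any informal late reporting could differ by arm as well.

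**Working it through.** **1. The plan's own figure.** Statistical considerations (2.5.2) assumes recurrence of 40% against 25%, 80% power and 5% significance (two-sided assumed here), and arrives at 155 per group. The log-rank calculation by Freedman's method gives a hazard ratio of ln(0.75)/ln(0.60) = 0.563 and 101 events, and 101/(0.40 + 0.25) = 155.4 per group. The figure is reproduced. The point does not depend on it, but the two rates are used below.

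**2. Windows side by side.**

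| Item | Section | Window stated |
|---|---|---|
| Adverse event collection | 2.4.6 | first procedure to month 6 |
| Visits | 2.4.7 | months 3, 6, 12 |
| Primary endpoint | 2.4.8 | 1 year |
| Death, stroke, bleeding, periprocedural events | 2.4.8 | none |
| Repeat ablation | 2.4.5 | no limit |

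Uncovered share for general adverse events: (12 − 6)/12 = 50% of follow-up.

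**3. Candidates for a repeat procedure.** With 340/2 = 170 per arm, expected recurrences are 170 × 0.40 = 68 (PVI alone) and 170 × 0.25 = 42.5 (combined arm), a ratio of 1.6 and a total of 110.5.

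**4. First recurrences after month 6, if the hazard is constant over months 3 to 12 (an assumption).** Months 3 to 6 are one third of that interval.
- PVI alone: 1 − 0.60^(1/3) = 15.7% by month 6, leaving 40 − 15.7 = 24.3% later.
- Combined arm: 1 − 0.75^(1/3) = 9.1% by month 6, leaving 25 − 9.1 = 15.9% later.
- Both arms: 170 × (0.243 + 0.159) = 68.3 of 110.5, or 62%.

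This counts first recurrences. It does not count repeat ablations or their complications.

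**5. First-year repeat ablations after month 6, under assumed timing.** Let L be the lag in months from recurrence to repeat procedure.
- Recurrences uniform over months 3 to 12, no repeats during blanking: share = 6/(9 − L). L = 0 gives 67%; L = 3 gives 100%.
- The same, with 30% of repeats during blanking: 0.7 × 67% = 47% to 0.7 × 100% = 70%.
- Front-loaded recurrences, F(t) = 1 − exp(−k(t − 3 − L)) with k = ln 2/half-life: share = (F(12) − F(6))/F(12). A half-life of 1.5 months with L = 0 gives 24%; a half-life of 6 months with L = 2 gives 80%.

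The overall range is about 24% to 100%. The low end needs early recurrence and almost no lag, which fits poorly with scheduled ECG detection starting at month 6. The article nevertheless gives no timing that would exclude it.

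**The case against.** The strongest counter-argument is that an adverse event rule is not an endpoint rule. Death, symptomatic stroke and bleeding are listed as endpoints separately from periprocedural adverse events. No section says they are captured only through adverse event reporting or that their ascertainment ends at month 6, and the 12-month visit could record all three. A reader might infer that half the deaths, strokes and bleeds are lost. The article does not support that, and this part of the objection stands.

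A reader might also infer that most repeat-ablation complications are lost. The article gives no number, timing or complication rate for repeat procedures, and the 62% rests on an assumed hazard and counts recurrences. Nor does the cut-off touch recurrent AF after repeat ablation: that is a rhythm outcome, covered by the month 6 to 12 monitoring. Both points stand.

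Next, periprocedural may refer to the index procedure alone. That is the randomised treatment, and 6 months is ample for its complications. The reading is possible, but the endpoint as worded covers any such event, and the protocol itself sets arm-specific rules for repeat procedures.

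The direction of any bias is also open. If harm follows the number of repeats, omitting it makes PVI alone look safer. The different lesions allowed in the combined arm could work the other way.

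Finally, a condensed article may leave endpoint windows to the full protocol. That explains why the endpoints have no window here. It does not answer the 6-month rule, which the article itself states.

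**Conclusion.** The point holds in limited form. The only stated collection window closes at month 6 of a 12-month follow-up, so general adverse events in months 6 to 12, including complications of repeat ablations in that period, fall outside it. For that stream the gap is half the follow-up.

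The loss may be uneven, because expected recurrence is 40% against 25% and the permitted repeat lesions differ. Neither the direction nor the size of the imbalance can be derived from the article. The share of repeat ablations affected depends on timing that the article does not give.

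The primary endpoint, sample size, alpha and power are unaffected. This is an inexpensive improvement to the safety comparison and does not threaten the main result.

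**What to change.** Amend Collection of clinical and follow-up data so that deaths, strokes, bleeding events, and serious or procedure-related adverse events are collected from the first procedure to month 12 in both arms, including events after any repeat ablation. The scheduled 12-month visit can carry this. Patients already past month 6 can have the interval covered at that visit.

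Align Study endpoints by applying the same 12-month window to the safety endpoints and by stating whether periprocedural events include those of repeat procedures.

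The cost is an amendment, an additional case report page at an existing visit, and a small amount of data entry. No design parameter changes.

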#### Follow‐up schedule

2.4.7

Patients will be followed at 3, 6, and 12 months after ablation. A 12‐lead ECG, Holter ECG, medication assessment, and blood tests will be acquired at 6 and 12 months. Transthoracic echocardiography will be performed at 12 months. Twice‐daily 30 s rhythm checks and symptom‐driven checks will be performed with portable ECG from 6–12 months.

#### Study endpoints

2.4.8

The primary endpoint of the study will be the recurrence of AF documented by scheduled or symptom‐driven ECG tests during the 1 year follow‐up period after the index ablation procedure. “Recurrence of AF” is defined as the documentation of any atrial arrhythmia including AF, AFL, and/or AT lasting ≥30 s by 12‐lead ECG or other appropriate tests. The endpoint will be determined by the endpoint committee, which will be composed independently of protocol developers, data and safety monitoring board, clinical research funders, investigators, subcontractors, and collaborators.

Secondary endpoints will include death from any cause, symptomatic cerebrovascular stroke, bleeding events, recurrent AF after repeat ablations, and any periprocedural adverse events. Bleeding events are defined as major bleeding in the ISTH bleeding criteria^17^ and bleedings needing for hospitalization.

### Study organization and status

2.5

#### Osaka Cardiovascular Conference

2.5.1

The Osaka Cardiovascular Conference (OCVC) consists of cardiologists belonging to the Osaka University Graduate School of Medicine or one of its 30 affiliated Osaka hospitals. The OCVC was initiated in 2014 to investigate clinical questions in the realm of cardiovascular medicine. Among participating institutions, physicians from seven hospitals that perform a large volume of invasive treatments for AF comprise the OCVC‐SUPPRESS‐AF investigators and are participating in this study.

SUPPRESS‐AF started enrollment in June 2019, and completion of enrollment is expected in March 2022. Completion of the study is expected by March 2023.

